# Effect of a multicomponent exercise program and cognitive stimulation (VIVIFRAIL-COGN) on falls in frail community older persons with high risk of falls: study protocol for a randomized multicenter control trial

**DOI:** 10.1186/s12877-022-03214-0

**Published:** 2022-07-23

**Keywords:** Falls, Physical exercise, Cognitive function, Fractures, Frailty

## Abstract

**Background:**

Falls represent important drivers of intrinsic capacity losses, functional limitations and reduced quality of life in the growing older adult’s population, especially among those presenting with frailty. Despite exercise- and cognitive training-based interventions have shown effectiveness for reducing fall rates, evidence around their putative cumulative effects on falls and fall-related complications (such as fractures, reduced quality of life and functional limitations) in frail individuals remains scarce. The main aim of this study is to explore the effectiveness program combining an individualized exercise program and an executive function-based cognitive training (VIVIFRAIL-COGN) compared to usual care in the prevention of falls and fall-related outcomes over a 1-year follow-up.

**Methods:**

This study is designed as a four-center randomized clinical trial with a 12-week intervention period and an additional 1-year follow-up. Three hundred twenty frail or pre-frail (≥ 1 criteria of the Frailty Phenotype) older adults (≥ 75 years) with high risk of falling (defined by fall history and gait performance) will be recruited in the Falls Units of the participating centers. They will be randomized in a 1:1 ratio to the intervention group (IG) or the control group (CG). The IG will participate in a home-based intervention combining the individualized Vivifrail multicomponent (aerobic, resistance, gait and balance and flexibility) exercise program and a personalized executive function-based cognitive training (VIVIFRAIL-COGN). The CG group will receive usual care delivered in the Falls Units, including the Otago Exercise Program. Primary outcome will be the incidence of falls (event rate/year) and will be ascertained by self-report during three visits (at baseline, and 6 and 12 weeks) and telephone-based contacts at 6, 9 and 12 months after randomization. Secondarily, effects on measures of physical and cognitive function, quality of life, nutritional, muscle quality and psychological status will be evaluated.

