**Secondary outcomes**							
Risk of falls Usual Gait Speed (UGS) Time up and Go (TUG)	X			X			
Short Physical Performance Battery (SPPB)		X	X	X			
Barthel index (BI)	X		X	X	X	X	X
Frailty Linda Fried criteria	X			X			
Montreal Cognitive Assessment (MoCA)		X	X	X			
Garvan fracture risk calculator		X		X	X	X	X
Yesavage GDS Scale		X		X	X	X	X
UGS with dual tasking		X	X	X			
Clinical criteria of sarcopenia		X		X			
Maximal isometric force of handgrip, knee extension and hip flexion		X	X	X			
Fear of falling (STAC)		X		X	X	X	X
Quality of life (EQ-5D)		X		X	X	X	X
Previous lifestyle		X					
Trail Making Test (TMT – Part A)		X	X	X			
1RM (Leg press)		X	X	X			
Muscular power at 50% 1RM in leg press		X	X	X			
Polypharmacy		X		X	X	X	X
Cumulative Illness Rating Scale for Geriatrics (CIRS-G)		X					
Mini Nutritional Assessment Test (MNA)		X					
Acceleration data: gait kinematic parameters (regularity, variability, cadence), Five Times Sit to Stand Test (peak power, impulse) and balance parameters (power spectrum, area)		X	X	X			
Muscular Echo intensity and thickness (ultrasound)		X		X			
Mortality		X	X	X	X	X	X
Admissions to emergency room and hospitalizations		X	X	X	X	X	X
Institutionalization		X	X	X	X	X	X

The multidisciplinary research team have well-known previous experience in functional geriatric assessment and in the prescription of exercise in frail aged participants in different clinical settings [71, 75, 76].

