#### Secondary outcomes

The secondary measures will be assessments that evaluate fall-related constructs such as fall-related healthcare system utilization, cognitive and physical capacities, psychological and muscle size and quality by echography. Additionally, instrumented measurements of frailty-related kinematic parameters will be performed during the physical performance measures by using inertial sensors (Table 1).

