### Fall risk

An increased risk of falling will be considered according to national and international recommendations (one or more of the following criteria): 2 or more falls or 1 fall with medical attention in the last twelve months or a significative gait disorder assessed by performance tests (TUG > 20 s and or UGS test < 0.8 m/s) [14, 86]. The TUG test is a classic test to assess risk of falls. Participant must raise from a chair without help, walk three meters, turn back and sit again. A time of > 20 s is indicative high risk of falls [87].

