### Fracture risk

Risk of fracture will be assessed with the Garvan fracture risk calculator (https://www.garvan.org.au). This tool allows to estimate 5- and 10-years fracture risk by equations based on anthropometric data, previous fractures since the age of 50, falls in the last year and optionally bone mineral density data. It has been validated very recently in Spanish population [93].

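### The abstract promises an effect on nutritional status, but the MNA is taken only at baseline; as smaller points, Garvan scores before 12 months count pre-randomisation falls, and two descriptions of the 12-week fall-risk outcome differ

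*Protocol article*

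**What the plan says.** **Nutrition.** The Methods paragraph of the abstract states, as a secondary aim, that "effects on measures of physical and cognitive function, quality of life, nutritional, muscle quality and psychological status will be evaluated". Table 1 (Study timeline) lists "Mini Nutritional Assessment Test (MNA" under its secondary outcomes heading, with one mark, at T0. The Secondary outcomes section of the body text names "fall-related healthcare system utilization, cognitive and physical capacities, psychological and muscle size and quality by echography"; nutrition is not among them, nor is it in the objectives that close the Introduction.

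**Garvan score.** Table 1 schedules the "Garvan fracture risk calculator" at T0, T2 (12 weeks), T3 (6 months), T4 (9 months) and T5 (12 months). The Fracture risk section gives its inputs as anthropometric data, earlier fractures, "falls in the last year and optionally bone mineral density data".

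**Fall risk.** The Fall risk section, placed among the outcome measures, defines increased risk as "2 or more falls or 1 fall with medical attention in the last twelve months or a significative gait disorder assessed by performance tests", the tests being TUG and usual gait speed. The Table 1 row reads "Risk of falls Usual Gait Speed (UGS) Time up and Go (TUG" and is marked at Screening and T2 only.

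**The concern.** A treatment effect on an outcome needs at least one measurement after randomisation. Nutrition has none, so the abstract announces a result that the trial cannot deliver as scheduled.

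The Garvan issue is one of timing. A score that looks back one year, taken less than one year after randomisation, counts some falls that the intervention could not have influenced. Those falls are expected to be alike in both arms, so they pull the fall component of the comparison toward no difference. A null Garvan result at 12 weeks would then say little about treatment.

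For fall risk, the two descriptions lead to different outcomes. The two performance tests reflect the participant's state at 12 weeks. The composite could keep a participant classed as high risk because of falls before enrolment, whatever happened under treatment.

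**Working it through.** The plan states no figure on this point, so there is none to reproduce. The checks are a reading of the schedule and a look-back calculation.

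**1. Post-baseline assessments, read from Table 1**

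- MNA: one mark (T0), so 0 after baseline.
- Garvan: T2, T3, T4 and T5, so 4 after baseline.
- Fall risk: T2, so 1 after baseline.

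No other row of Table 1, and no paragraph of the outcome sections, describes a nutritional measure. The MNA count of 0 therefore settles the nutrition point.

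**2. Share of a one-year look-back that precedes randomisation**

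For an assessment t years after randomisation, the share is 1 − t. The abstract times the telephone contacts from randomisation. The Data collection section times them from the start of participation. I take the two as the same date, and count the 12-week visit from it too.

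- T2: (52 − 12)/52 = 40/52 = 77%
- T3: (52 − 26)/52 = 50%
- T4: (52 − 39)/52 = 25%
- T5: (52 − 52)/52 = 0%

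Three of the four post-baseline Garvan assessments reach back before randomisation. Only T5 does not.

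**3. What this does to the fall count in the window (illustration only)**

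The Sample size and statistics section assumes 1.8 falls/year under usual care and a 30% reduction, which gives 0.70 × 1.8 = 1.26 falls/year under the intervention. The pre-randomisation rate p is not given; I assume 1.8 to 3.5 falls/year. The rate ratio seen in the window is

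[p(1 − t) + 1.26t] / [p(1 − t) + 1.8t].

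- T2, p = 1.8: (1.385 + 0.291)/(1.385 + 0.415) = 0.93; p = 3.5: (2.692 + 0.291)/(2.692 + 0.415) = 0.96
- T3, p = 1.8: (0.90 + 0.63)/(0.90 + 0.90) = 0.85; p = 3.5: (1.75 + 0.63)/(1.75 + 0.90) = 0.90
- T4, p = 1.8: (0.45 + 0.945)/(0.45 + 1.35) = 0.78; p = 3.5: (0.875 + 0.945)/(0.875 + 1.35) = 0.82
- T5: 1.26/1.8 = 0.70 for any p

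These ratios describe the number of falls in the window. They are not the effect on the Garvan score, because the documents do not give the weight of falls in that score.

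**4. Fall risk, side by side**

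The Fall risk section combines a 12-month fall history with gait tests, joined by *or*. The Table 1 row names usual gait speed and TUG only, and neither has a look-back. If the composite is the T2 outcome, the 77% above applies to its fall-history part. If the two tests are the outcome, no look-back arises.

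**The case against.** **On nutrition,** the promise stands in one abstract sentence. The objectives and the Secondary outcomes text do not repeat it, and Table 1 also places other baseline-only items (previous lifestyle, CIRS-G) under the same heading. The MNA may always have been meant as a descriptor. That explains the single mark, but it does not remove the conflict: neither of those other items is announced as an effect, and nutrition is. What stands of the objection is that the point is small and may need only a wording change.

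**On Garvan,** the look-back belongs to an existing calculator and is not a drafting error. Falls before randomisation are balanced in expectation, 12 months is already scheduled, and the choice of time point is commonly left to the analysis plan. All of this stands, and it makes Garvan a secondary point. A reader might infer that the early comparisons are biased, or that 77% of the Garvan effect is lost at 12 weeks. The documents support neither: the mechanism is dilution, and 77% is a share of the window, not of the score. Restricting the comparison to 12 months also has a drawback, because the fall input then covers the same year as the primary outcome.

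**On fall risk,** a reader might infer that this outcome too is contaminated from 12 weeks to 9 months, or that participants enrolled on fall history cannot improve on it. Table 1 does not support the first, because fall risk is re-assessed at T2 only. The second holds only if the composite is the outcome, and the Table 1 row points to the two tests. The documents also do not give the share of participants enrolled on falls rather than gait.

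**Conclusion.** The nutrition point holds on the text alone: an effect is announced, there are 0 post-baseline measurements, and the effect cannot be estimated.

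The Garvan point holds in limited form. At 12 weeks, 6 months and 9 months, about 77%, 50% and 25% of the fall look-back lies before randomisation. This dilutes the fall component without biasing it. The shares rest on the visit clock starting at randomisation. The size of the dilution in the score cannot be derived from the documents.

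The fall-risk point is no more than a need to reconcile the Fall risk section with the Table 1 row for the single 12-week re-assessment.

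**What to change.** 1. **Nutrition:** either add the MNA at T2, or remove nutrition from the effects listed in the abstract and label the MNA a baseline descriptor. The first costs one short questionnaire at a visit that already takes place. Recruitment began in July 2021, so participants already past week 12 would have no follow-up value, and the analysis would have to say so. The second costs a wording change.
2. **Garvan:** base the between-group comparison on T5, where the look-back equals the randomised year, and treat T2 to T4 as descriptive. State that the T5 fall input overlaps with the primary outcome, so a Garvan difference is not independent confirmation. No new data are needed. The cost is reliance on the latest time point, where the planned 20% withdrawal during follow-up has had the longest time to build up.
3. **Fall risk:** state that the T2 outcome is TUG and usual gait speed, as the Table 1 row lists, and that the composite with fall history is not re-applied at T2 as an outcome. This costs one sentence.

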**Discussion:**

This trial will provide new evidence about the effectiveness of an individualized multidomain intervention by studying the effect of additive effects of cognitive training and physical exercise to prevent falls in older frail persons with high risk of falling. Compared to usual care, the combined intervention is expected to show additive effects in the reduction of the incidence of falls and associated adverse outcomes.

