The OTAGO exercise program (OEP), that was developed in the 1960s in New Zealand [57], is considered the gold-standard exercise-based intervention in falls prevention. It consists of several strength, endurance, flexibility and balance exercises supervised by a physical therapist. It has shown to be effective in improving fall-related risk factors [58–60] and preventing falls [61, 62] and related consequences [63, 64]. Notably, several adaptations have been performed since it was firstly designed, leading to a high degree of heterogeneity, with mixed results obtained from different delivery fashions [65–67]. In addition, falls and fall-related outcomes have been poorly registered in available studies, and how exercise programs impact fall-related fractures, healthcare utilization, psychological and social issues remains scarcely investigated [68]. Consequently, well-powered studies with long follow-up periods and comprehensive evaluation of falls consequences are needed in order to capture the real potential of exercise programs in different populations of older adults [42].

Recently, the VIVIFRAIL Project (www.vivifrail.com) was developed by world experts in the field of physical exercise and frailty aiming to provide necessary knowledge to prescribe individualized physical exercise in the prevention of frailty and falls in older persons. Within the VIVIFRAIL philosophy, exercise prescription is based on the functional status and fall risk of the individual, evaluated through performance-based measures [69]. This approach aligns with the recently proposed function-based healthy ageing paradigm [70]. So far, this exercise program has been proven safe and effective to reverse the hospitalization-associated functional decline in very old patients [71] and to promote functional gains in cognitively impaired frail community-dwellers [72], but its effectiveness to reduce falls and health related-consequences, and whether its combination with cognitive training have added effects remain uncertain.

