In this context, the main objective of this study is to evaluate the effectiveness of a combined individualized multicomponent exercise and cognitive training (VIVIFRAIL-COGN) program on the reduction in fall-incidence in a sample of community-dwelling frail older adults with high fall risk, compared to usual care (including the OEP). Secondarily, we will investigate the impact on fall-related consequences, such as need for medical assistance, psychological issues (fear of falling and depression), physical and cognitive capacities and quality of life.

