### Detailed description of the intervention

#### Usual care group (control group)

Participants randomized to the control group will receive normal outpatient care in the Fall Unit. Briefly, it includes a detailed multidimensional assessment performed by the multidisciplinary team (geriatrician, nurse, physiotherapist, occupational therapist) to identify potential intrinsic and extrinsic factors related with falling. Frequently, causality of falling is multifactorial and interventions in the Falls Units are based on the identification of individual risk factors. General approach includes medical review of high risk of falling medications, nutritional interventions like vitamin D in deficient patients, environmental modifications and prescription of the OEP, deemed the gold-standard exercise program in falls management and therefore, part of the usual care delivered to frail older fallers.

Subjects in this group will partake in a home-based exercise program based on the OEP lasting 12-weeks. A physiotherapist will provide a comprehensive explanation of the program, as well as fall risk, safety and adherence information at the baseline visit and will monitor progression during the study visits. Subjects will be encouraged to perform cardiovascular, strength, flexibility and balance exercises 3-times/week. Both volume and intensity will be adjusted by the physiotherapist based on participant’s self-reported feelings. Subjects will be provided with a booklet with instructions (Additional File 1) and an adherence log (Additional File 2) that will be filled in by the participant or a proxy.

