#### Intervention group (VIVIFRAIL-COGN)

Participants assigned to this group will participate in a 12-week home-based program combining the VIVIFRAIL multicomponent physical exercise and an individualized cognitive training programme (VIVIFRAIL-COGN).

B1- Multicomponent VIVIFRAIL exercise group

The multicomponent physical exercise program will be based on the VIVIFRAIL programme which was developed in Europe (Erasmus + programme of the European Union).

The VIVIFRAIL multicomponent exercise intervention program includes individualized sets of resistance training, gait and balance training, which appear to be the best strategy for falls rate reduction in older individuals and to maintaining functional capacity during ageing [78]. This type of intervention has also been proven as the most effective to delay disability, cognitive impairment and depression [79] as well as effective to reverse the functional decline associated with acute hospitalization in very old patients [71]. The VIVIFRAIL exercise program was originally designed with the aim of providing guidance in exercise prescription to professionals managing frail older adults with or without falls older than 70 years [78]. The programme is tailored to the older person’s functional capacity evaluated by the SPPB and a UGS test and the risk of falling, aligning with the new functional-based older adult’s health perception proposed by the WHO [70] Different standardized programs oriented to the functional level of the individual were designed and description of the performance, intensity, volume, frequency and monitoring are described in the materials published. Recently, a new user-friendly simplified version and a simple mobile app with interactive videos have been produced to ease adoption and maximize adherence. (see www.vivifrail.com).

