In every session a combination of one exercise from Set A (attentional activities) and one exercise from Set B (executive function activities) will be performed (see Table 3). An initial training session will be performed to explain the programme to the participants and their relatives or caregiver (the support of one person during sessions will be needed due to characteristics of the cognitive training exercises).

To guarantee adherence to the program and appropriate execution of cognitive training exercises, a videoconference session will be performed at week 3 and 9 of the program by the occupational therapists. The purpose of this monitoring is to resolve doubts, adapt difficulty and provide support.

Either the participant and the companion will be instructed in the general and individual characteristics of both physical and cognitive programs (VIVIFRAIL-COGN). Also, all participants will receive instructions, printed materials and audiovisual support of the cognitive sessions with the VIVIFRAIL-COGN material.

Table 4 shows the recommended distribution of both the physical and cognitive components of the intervention. Adherence to the cognitive training program will be registered together with the exercise in the VIVIFRAIL booklet.

**Table 4 Tab4:** Recommended distribution of exercise and cognitive training sessions per week

	**Monday**	**Tuesday**	**Wednesday**	**Thursday**	**Friday**	**Saturday**	**Sunday**
Morning	VIVIFRAIL Wheel	Walk	VIVIFRAIL Wheel	Walk	VIVIFRAL wheel	Walk	Rest
Afternooon		Cognitive training		Cognitive training			

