Nowadays healthcare actions to prevent falls in frail older persons with high risk of falling remain scarce, isolated and usually fragmented, despite the efforts that are being made by policymakers, reflected in the recent availability of evidence-based public national/international recommendations [12, 73, 86]. In those recommendations, physical exercise appears as the most evaluated intervention. It is very well known that it is an effective and safe intervention to reduce risk and rate of falls [37, 41, 42]. Our research group very recently showed that the VIVIFRAIL program (www.vivifrail.com) [75] is feasible and effective to improve functional capacity in frail older persons with cognitive problems [72] but we did not explore its potential in falls prevention. It is possible that more integrated and multidomain interventions, as proposed in the present study protocol, are needed in the case of frail older persons. Specifically, if our hypothesis is correct and we show that VIVIFRAIL-COGN intervention is more effective in terms of rate, risk of falls and functional improvement in this population, a new therapeutic window is opened: falls and risk of falls may be improved (and potentially the burdensome consequences of falls, such as fractures) through combined physical-cognitive interventions.

One of the strengths of our study is the multidisciplinary nature of the project (geriatricians, physiotherapists, occupational therapists, psychologists, nurses). This is a remarkable opportunity to establish new protocols and share our results with the scientific community and healthcare professionals with interest in frail older persons with high risk of falling.

Another important aspect of our study is the non-exclusion of frail older patients with cognitive problems. Falls are very prevalent in cognitive decline frail older persons and cognitive decline it is a very well-known risk factor of falling and fractures. The non-exclusion of frail participants with high risk of falling and cognitive problems improves external validity and makes the trial unique in comparison with previous trials in this research area.

In summary, this trial will provide new evidence about the effectivity of an individualized multidomain interventions on falls by studying the effect of additive effects of cognitive training and physical exercise to prevent falls in older frail persons with high risk of falling.

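### Two arms that differ in both exercise programme and cognitive training cannot show the additive effects that the Abstract and Discussion say the trial will study

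*Protocol article*

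**What the plan says.** **The claim.** The Abstract's Discussion paragraph says the trial will supply evidence by studying additive effects of the two components, and then that "the combined intervention is expected to show additive effects in the reduction of the incidence of falls" relative to usual care. The last paragraph of the main Discussion, before Dissemination, repeats that the evidence will come "by studying the effect of additive effects of cognitive training and physical exercise to prevent falls".

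**The gap it answers.** The Background, having described VIVIFRAIL, says that "whether its combination with cognitive training have added effects remain uncertain".

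**The design.** The Abstract's Methods paragraph states: "They will be randomized in a 1:1 ratio to the intervention group (IG) or the control group (CG"). The intervention arm receives a "12-week home-based program combining the VIVIFRAIL multicomponent physical exercise and an individualized cognitive training programme (VIVIFRAIL-COGN"). For the control arm: "Subjects in this group will partake in a home-based exercise program based on the OEP lasting 12-weeks". The cognitive component has its own introductory session for participant and caregiver, and "a videoconference session will be performed at week 3 and 9 of the program by the occupational therapists".

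**The objective and analysis.** The main objective, at the end of the Background, is to evaluate the combined programme "compared to usual care (including the OEP"). The section Sample size and statistics plans a negative binomial regression with randomized group as the exposure.

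**The concern.** An additive or added effect of cognitive training is a statement about one component given on top of another. Estimating it needs at least one comparison in which the exercise is held fixed and cognitive training varies. Here both change together: controls do an Otago-based programme without cognitive training, and the intervention arm does VIVIFRAIL with it. Two passages thus attach to the trial an inference that its design cannot deliver, while the stated objective asks a different question that the design can answer.

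What is at stake is attribution. The Discussion looks ahead to a new therapeutic window through combined physical-cognitive interventions, and Future directions looks ahead to wider roll-out. A reader who takes the additive wording at face value could credit cognitive training with a benefit that came wholly from using VIVIFRAIL in place of Otago.

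**Working it through.** **1. What each arm receives**

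| | Intervention arm | Control arm |
|---|---|---|
| Exercise | VIVIFRAIL, 12 weeks, home-based, 3 sessions/week | Otago-based, 12 weeks, home-based, 3 times/week |
| Cognitive training | Twice weekly, with a training session and two videoconferences | None described |
| Other Falls Unit care | Not the subject of the contrast | Multidisciplinary assessment and management |

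The exercise programmes overlap in domains and frequency but are not the same. VIVIFRAIL is assigned by functional level. Its balance-reinforced version is triggered by fall-risk criteria that include every route by which a participant can meet the trial's own high-risk entry criterion, so essentially all intervention participants would receive it. Table 4 also recommends walking on three further days.

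**2. What the contrast identifies**

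Write the log fall rate as

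log rate = m + a·[VIVIFRAIL rather than Otago] + b·[cognitive training] + g·[both].

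- Control arm: m.
- Intervention arm: m + a + b + g.
- Contrast: a + b + g.

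This is one estimable quantity with three unknowns. The two cells needed to separate them (VIVIFRAIL without cognitive training, Otago with it) are not observed. Even if g = 0 is assumed, which is what additivity means on this scale, two unknowns remain. Additivity on any other scale needs the same missing cells. More participants make the sum more precise and do not split it.

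**3. The plan's own figure**

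Inputs from Sample size and statistics: 1.8 falls/year in controls, a 30% reduction (1.8 × 0.70 = 1.26), mean follow-up 0.9 years, alpha 5% (taken as two-sided), power 80%, 129 per group. The dispersion k is not given.

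n per arm = (1.960 + 0.842)² × [(1/0.9)(1/1.8 + 1/1.26) + 2k] / (ln 0.70)²

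This gives 93 at k = 0, 124 at k = 0.25 and 155 at k = 0.5. The stated 129 corresponds to k = 0.296, so it is attainable but cannot be strictly reproduced. It powers the package contrast only, and the point does not depend on it.

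**4. How far one result leaves the components open**

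Take g = 0 and an observed ratio of 0.70, so that 0.70 = (VIVIFRAIL vs Otago) × (cognitive add-on):

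| VIVIFRAIL vs Otago | Cognitive add-on |
|---|---|
| 1.00 | 0.70 |
| 0.90 | 0.778 |
| 0.80 | 0.875 |
| 0.70 | 1.00 |

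Every row gives the same trial result.

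**5. What a direct estimate would take (illustration only)**

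With k = 0.296 assumed and a hypothetical VIVIFRAIL-only arm as reference, the same formula gives the number per arm, before withdrawal, for 80% power on the add-on: 129 if VIVIFRAIL vs Otago is 1.00, 269 if it is 0.90, and 989 if it is 0.80. The question is separate from the one the trial is sized for.

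**The case against.** **The strongest reply** is that nothing operative rests on the phrase. The main aim, main objective, sample size and analysis all compare the package with usual care. The Discussion opens by comparing the programme with a standard intervention, and its anticipated conclusion concerns combined interventions. No interaction or additivity analysis is planned. The Abstract says only that additive effects are expected, and since that sentence is framed against usual care, it could mean extra benefit over care that already includes exercise.

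Most of this stands, and it limits the point to wording. It does not remove the point. The statement that the trial works by studying additive effects appears in both the Abstract and the closing summary without that softening. The component sense is also the document's own: the Abstract's Background names cumulative effects of the two kinds of training as the gap, and the Background contrasts combined training with motor training alone.

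**Stronger readings that a reader might infer** are not supported:

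- *That the arms have no exercise in common, or differ broadly in contact and materials.* Both programmes are 12-week, home-based, three times weekly, and cover aerobic, strength, balance and flexibility work. Controls also receive a physiotherapist's explanation, monitoring at visits, a booklet and an adherence log. Ankle weights are mentioned for the intervention arm, but the control section does not say whether controls receive them. The contact differences the text supports are the cognitive training session and the two videoconferences, which are part of delivering that component.
- *That a null result would be misread.* That concerns the active comparator, which is openly disclosed, and not additivity.
- *That an adherence-based component analysis needs relabelling.* Cognitive adherence is recorded, but no such analysis is described.

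**Conclusion.** The point holds as a mismatch between stated inference and design. The trial yields one rate ratio for the package. The effect of adding cognitive training to exercise, and any additivity of the two, is not identifiable at any sample size. Under a multiplicative split, with neither component harmful, a package ratio of 0.70 leaves the cognitive add-on anywhere between 0.70 and 1.00. Non-identifiability itself needs neither assumption; it follows from two arms that differ in both exercise programme and cognitive training.

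A reader might go further and infer that the design or the primary analysis is faulty. The documents do not support that. Comparing a package with active usual care is a legitimate choice, the main objective describes it correctly, and that comparison remains valid.

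**What to change.** In the Abstract's Discussion paragraph (both sentences) and in the closing summary of the main Discussion, replace the additive-effects wording with the effect of the VIVIFRAIL-COGN package compared with Falls Unit care including the Otago programme. Add one sentence stating that the separate contribution of the cognitive component cannot be estimated from this design. The Background sentence on the open question can stay as motivation, provided the text does not imply that this trial resolves it.

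The cost is a narrower claim. Arms, sample size, outcome and analysis are unchanged.
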